#### Secondary outcome measures

Proportion of the population with a chronic cough on salbutamol/corticosteroid inhaler indicated in their health passports.Proportion of the population with a chronic cough with a diagnosis of TB or airway disease among patients with chronic cough attending primary health care recorded in patient registers at intervention facilities.Proportion of people with disabilities with a diagnosis of TB or airway disease recorded in their health passports in all arms of the study.

In order that diagnoses of CAD, including asthma and TB are made with a high level of accuracy, appropriate merit-based training of spirometry technicians will be done by a competent (PATS/ERS/ATS) certified trainer. Spirometry technicians will further undergo refresher training during the trial. Diagnosis of TB will be based on the routine practice of TB microscopy and chest X-rays (CXRs). In some instances the Gene Expert test will be performed according to an available standard algorithm. We will consider to undertake a systematic investigation of the accuracy of diagnoses made in a subset of patients by checking results, clinical notes in patient health passports, and CXR’s, along with a thorough clinical review.

Limitations for diagnosis include lack of sputum culture for TB diagnosis and computed tomography (CT) scan for conditions like bronchiectasis. Unfortunately sputum culture and CT scans are beyond the funding scope of the study.

### Case report forms

Electronic case report forms (CRFs) programmed onto smartphones using Open Data Kit (ODK) will be used to make the large number of CRFs manageable and provide real-time data entry, internal validity and consistency checks. CRFs will be treated as confidential documents and held and backed up on two secure servers. Data will be anonymised prior to analysis.

### Potential risks to the safety of the trial participants

Trial participants will be recruited from populations living in poor conditions in Malawi who live with relatively high day-to-day risks. The interventions are particularly low-risk and targeted at improving access to medical care for those at need. Overall we anticipate that participation in the trial will reduce risks to participants.

### Adverse event reporting

An adverse event (AE) is any unfavourable and unintended sign, symptom, syndrome or illness that develops or worsens during the period of observation in the study. A Serious Adverse Event (SAE) is an AE following the intervention that results in a) death, b) a life-threatening AE, c) hospitalisation or prolongation of an existing hospitalisation, d) disability or incapacity, e) congenital anomaly in the offspring of a participant.

The interventions we will be using in this trial are particularly low-risk interventions that offer potential safety benefits (e.g. improved access to care). Nevertheless, we will collect data about AEs. Data about AEs that are not serious will be collected with the population-based survey at the end of the trial. Participating health centres will be asked to report SAEs in relation to the interventions immediately to the trial coordinating centre. The trial coordinating centre will collect details about the SAE using a pro-forma in accordance with a specific standard operating procedure (SOP). This information will then be passed immediately to [name] who will conduct a causality assessment (not related/improbable, possible, probable, definite), assess seriousness and expectedness, take any appropriate medical action and inform the College of Medicine Research Ethics Committee (COMREC) and the Liverpool School of Tropical Medicine Research Ethics Committee (LSTM REC) of any events deemed related to the trial intervention within 7 days of knowledge of the event. All other SAEs will be reported as part of an annual report to COMREC and LSTM REC. All SAEs that relate to the interventions will be followed to resolution.

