### Trial sites

The trial sites will be in the districts of Dowa and Ntchisi, in the central region of Malawi. A total of 27 primary health centres in the districts will be involved in the trial. Each cluster will include a primary health centre together with the surrounding catchment area. To reduce contamination between clusters there will be a 3-km buffer zone between each cluster. The health facilities have been selected based upon their size according to the number of health workers and type of service offered. Those with in-patient services have been excluded. There are 11 such health centres in Ntchisi and 16 in Dowa district. Private not-for-profit health facilities, which run under the Christian Health Association of Malawi (CHAM), have been included.

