#### The interventions

*Intervention arm 1* – Health centres implementing the PAL intervention. No informal provider intervention.*Intervention arm 2 –* Health centres implementing the PAL intervention. Informal provider intervention.*Control arm –* No intervention at health centre or informal provider level. Routine standard care will be provided.

#### Detail of the health centre-based PAL intervention in arms 1 and 2

The intervention at health centres will involve training medical assistants and nurses on the PAL guide-lines and use of spirometry for the diagnosis and assessment of airflow limitation in patients presenting with chronic cough. The trial will test the feasibility of implementing PAL strategy and integrating TB screening and CAD at the lowest level in the health system in Malawi. Lessons learnt are expected to influence policy and practice countrywide.

Other indicators to measure impact of the trial will include: occurrence and frequency of hospitalisations due to exacerbations, time lapse between symptom development and diagnosis. For TB patients, changes in this diagnostic delay may be a proxy indicator of health outcomes.

Training of health care providers will include:Training of health centre staff on identifying and managing TB and CADs from amongst those with chronic cough.Introducing the use of standardised registers for patients presenting with chronic cough.Introducing the syndromic approach and spirometry for the diagnosis of airway diseases and TB among patients with chronic cough.Introduction and uninterrupted use of inhalers (bronchodilators and corticosteroids) for patients diagnosed with asthma.Introduction and uninterrupted availability and use of inhalers (bronchodilators) for patients diagnosed with COPD.

The aim is that after training the medical assistants and nurses in the intervention health centres will competently carry out the following tasks:Screen and identify COPD, bronchiectasis, TB and asthma cases among patients presenting with chronic cough to primary health care facilities.Use appropriate screening and diagnostic tools and specimens for the diagnosis of COPD, bronchiectasis, TB and asthma.Make appropriate referral of patients to, and receive corresponding feedback from, secondary referral health facilities in the districts.Perform accurate recording and reporting of all cases using tools for the PAL guidelines.Provide key health messages about TB and CAD as part of the routine health talks.

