#### Consideration of potential risks to participating health centres and their catchment populations

The interventions being tested in this cluster level randomised trial are applied at a community or health centre level. At a community level, this is a signposting system and does not involve any treatments. At the health centre level we will be implementing an advanced care package that only contains components that would be considered standard good practice. At intervention health centres, each individual will, therefore, be managed with standard care and the additional diagnostic capabilities and treatments. Training will be given on the management of CAD and TB including managing any side effects of inhalers. As neither of the interventions are medications we have not included specific criteria for the modification or discontinuation of interventions. Individual treatments that have been initiated at the health centres can be discontinued by the patients at any time. There are no restrictions on the concomitant care that participants may receive during the trial.

If patients receive a diagnosis of CAD they may be given either salbutamol and/or corticosteroid inhalers, these have minimal side effects. Salbutamol inhalers may lead to a transient increase in heart rate, decreased plasma potassium concentration and decreased diastolic pressure. Side effects of corticosteroid inhalers include oesophageal candidiasis, dysphonia, wheezing and cough. Prolonged use of inhaled corticosteroids may increase the risk of developing TB in patients who are being treated for COPD [27]. Although the drugs used in this study are routinely used in health facilities in Malawi, the study will closely monitor and document any reported side effects and where possible the frequency of intake of these drugs may be reduced. Health facility staff will manage the side effects and refer to the district hospital if appropriate. Furthermore, adequate training in the use of inhalers and corticosteroids and side effects recognition will be given to minimise the occurrence of these side effects. Training on use of spirometers for diagnosing airflow limitation will also be given. This training will be facilitated by a chest specialist ([name]) who is part of this study.

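### Serious events are reported only by out-patient health centres and the household survey is kept to non-serious ones, so admissions and deaths elsewhere may go unreported and SAE counts would not be comparable between arms

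*Protocol article*

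**What the plan says.** All references are to the protocol article.

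- **Definition (Adverse event reporting).** "A Serious Adverse Event (SAE) is an AE following the intervention that results in a) death, b) a life-threatening AE"; the remaining criteria are "hospitalisation or prolongation of an existing hospitalisation" and "disability or incapacity, e) congenital anomaly in the offspring of a participant".
- **Who reports.** The same section asks participating health centres to report at once those SAEs that are connected with the interventions. No other reporter is named. For the rest it says: "Data about AEs that are not serious will be collected with the population-based survey at the end of the trial".
- **Who the reporters are (Trial sites; Selection criteria).** All 27 centres are out-patient only: "Those with in-patient services have been excluded".
- **Where sicker patients go (Consideration of potential risks to participating health centres and their catchment populations).** "Health facility staff will manage the side effects and refer to the district hospital if appropriate". The district hospital has no stated reporting role.
- **Feedback and supervision.** Among the tasks for trained staff at intervention centres is to "receive corresponding feedback from, secondary referral health facilities in the districts" (The interventions). Routine visits by the clinical supervisor are described for intervention facilities (Data collection and management).
- **What is promised.** SAEs not judged related go into an annual report to both ethics committees (Adverse event reporting). Every SAE goes to the trial steering committee (Research governance arrangements).
- **A further use of admissions.** The impact indicators include "occurrence and frequency of hospitalisations due to exacerbations" (The interventions), with no data source stated.

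**The concern.** The article divides safety capture into two channels. Serious events go to facilities that cannot admit a patient. The population-based source, which does not depend on the health centre, is left with the non-serious events. An admission always takes place outside the named reporters, and a death may well do so.

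The routes by which a centre might hear of such an event are also described more fully for arms 1 and 2 than for control. A difference in SAE counts between arms, or the lack of one, could then reflect how events were found and not how often they occurred.

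This matters because the trial has no data monitoring committee and no interim analysis. SAE reporting is therefore its main running safety check. The hospitalisation indicator also needs a source that covers all three arms, and none is named.

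**Working it through.** The article gives no SAE rate, admission rate or capture probability, so there is no figure to reproduce. The check sets the stated routes side by side.

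**Routes by which an admission or death could come to light**

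1. *Report by the health centre* (Adverse event reporting). Asked of all participating centres, but limited to SAEs connected with the interventions. Of the 27 centres, 0 have in-patient services.
2. *Referral by centre staff* (Consideration of potential risks). Staff know whom they sent to hospital. They do not thereby know the outcome, or who went there directly.
3. *Feedback from secondary facilities* (The interventions). A task for trained staff in arms 1 and 2; not described for control.
4. *Supervisor visits covering passports, registers and spirometry records* (Data collection and management). Intervention facilities; not described for control.
5. *Records kept by informal providers, with feedback from local services* (Detail of the informal health provider intervention). Arm 2 only.
6. *Three-monthly internal monitoring with health-passport verification* (Research governance arrangements). Not limited by arm, but described as quality control and given no SAE role.
7. *End-of-trial household survey* (Adverse event reporting). All three arms, same method; assigned to non-serious events.

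Routes 3 to 5 are described for intervention clusters only. Of the routes not limited by arm, the survey is the only one that reaches households directly, and it is assigned away from serious events.

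**Wording**

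An SAE must follow the intervention. Read strictly, nothing in the control arm qualifies, since that arm receives none. Centres report only intervention-connected SAEs, yet the annual report covers the unrelated ones and the steering committee is to receive all. The later promises need wider capture than the reporting instruction provides.

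**Share of reports from the intervention arms**

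With equal true rates, equal arm sizes and a ratio r of capture per intervention arm to capture in control, the two intervention arms supply 2r/(2r + 1) of all reports:

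- r = 1: 2/3 = 67 %
- r = 2: 4/5 = 80 %
- r = 5: 10/11 = 91 %
- no capture in control: 100 %

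The values of r are assumptions. With 18 of 27 clusters in intervention arms, a two-thirds share is expected even under unbiased reporting. Any imbalance must therefore be judged per arm.

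**Reach of the survey**

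27 clusters × 30 villages × 14 households = 11,340 households, or 3,780 per arm; × 2.4 = 9,072 individuals per arm. This agrees with the article. If 1 %, 2 % or 4 % were admitted in a year (an assumption; the article gives no rate), the survey would reach about 91, 181 or 363 people admitted per arm. These are all-cause admissions in the sample, not SAEs caused by the interventions. They show only that the source is large enough to be useful.

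**The case against.** The strongest reply has four parts.

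- **Centres are not blind to admissions.** Staff refer patients themselves, passports are verified every three months, and the harms the article discusses are inhaler side effects in patients treated at these same centres. This stands in part. Being unable to admit is not the same as being unable to learn of an admission, and referral feedback is not the only route. But the remaining routes are partial, and several are described only for intervention facilities.
- **Detail may sit elsewhere.** The article condenses a fuller protocol and cites an SOP that is not shown. This is a real limit. However, the SOP is cited for how the coordinating centre collects details of an SAE once it has been reported. The division of serious and non-serious events between two channels is stated in the article itself.
- **No comparison of SAEs between arms is planned, and routine care may include feedback.** True as far as the text goes. The article does not say that control centres lack feedback, and it nowhere says that a low count will be taken as proof of low risk. The point is that the counts could not bear such a reading.
- **A recall survey cannot serve immediate reporting or the 7-day notice.** Correct; it can only supplement them.

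A reader might also infer that most SAEs would be missed, or that those found would come mainly from the intervention arms because of biased capture. The documents support neither. Hospitalisation and death are two of five criteria, and no frequencies are given. Two of the three arms are intervention arms in any case.

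**Conclusion.** The point holds as a gap in where serious events are captured. The sole named SAE reporters are out-patient-only centres, and the one source applied alike in all arms is kept to non-serious events. Admissions and deaths elsewhere may go unreported. Feedback and supervision are described only for intervention facilities, so per-arm SAE counts would not be comparable. Separately, the instruction to report intervention-connected SAEs does not fit the promises to report all of them, and the sections must be reconciled.

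The size of the loss is unknown: depending on what is assumed, the share missed could lie anywhere from 0 to 100 %. The conclusion rests on what the article states and assumes that the SOP adds no further means of detection. It does not touch the primary outcome. The sponsor should correct it, because the change is small and running safety oversight depends on this route.

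**What to change.** 1. In Adverse event reporting, remove the restriction of the follow-up survey to non-serious events.
2. Add to the electronic follow-up form, identically in all three arms, household items on any admission (place, month, main reason) and any death of a member aged 15 or over since the interventions began. Tabulate both by arm.
3. Name these items as the source for the hospitalisation indicator.
4. State that referral feedback, or a health-passport entry showing an admission, triggers an SAE report in every arm, control included.
5. Reconcile the SAE definition and the instruction to centres with the annual report and the reports to the steering committee, so that it is clear whether all SAEs or only intervention-connected ones are to be captured, and what counts in the control arm.
6. Say that the survey supplements immediate SAE reporting and does not replace it.

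The cost is a few items on an existing form, a short amendment and slightly longer interviews. Recall over 12 months is imperfect, and in an open trial it may differ by arm, so the survey counts need that caveat. They also cover sampled households only.

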### Sample size and sampling approach

The primary objective of this study is to measure the impact of the interventions on the proportion of chronic cough patients with a diagnosis of CAD or TB in their health passport. The preliminary sample size considerations set out below are based solely on expert opinion; these assumptions and estimations for the follow-up impact study will be revisited in light of the data collected during the baseline survey.

#### Baseline survey

Data on CAD is not routinely collected in the study districts, so to inform the final sample size estimation a baseline survey will be conducted, the purpose of which will be to estimate the proportion of individuals over the age of 15 years in each cluster with (a) evidence of chronic cough-/- wheeze, and (b) a diagnosis in their health passport.

For this baseline survey, it will be assumed that for the study population:(i)the mean household size in the study area will be 4.6(ii) the proportion of individuals over the age of 15 years will be 0.52 (52 %)(iii) so the average number of individuals per household over the age of 15 years will be 4.6 × 0.52 = 2.4

As described in detail in table 1, a 3-stage sampling procedure will be used:Stage 1: a random sample of 27 clusters (health centres with surrounding catchment areas) will be selected and 9 of these randomly allocated to each study armStage 2: 30 villages will be randomly selected from each of these 27 clusters based on sampling probabilities proportional to village population again using Google Earth Pro (Google Inc., Mountain View, CA, USA) to identify villages and to estimate their sizes (total 810 villages: 270 per study arm)Stage 3: a simple random sampling procedure will be applied to select 7 households from each selected village (total 5,670 households: 1,890 per study arm)

All eligible participants in each selected household will be interviewed, giving a total sample of 5,670 × 2.4 = 13,608 individuals (4,536 per study arm); 10 % of these individuals (1,360 in total: 453 per study arm) will be expected to show evidence of chronic cough-/-wheeze.

The precision figures quoted below for this baseline survey use the approximate formula for a 95 % confidence interval ‘1.96 × standard error of prevalence estimate’. In the actual analysis, exact binomial confidence intervals will be computed, but these are asymmetric so unsuitable for presenting a simple indication of the precision levels that will be achieved.

Assuming a prevalence of 10 %, a sample of 4,536 individuals will provide an estimate of the true prevalence of chronic wheeze-/-cough in each individual study arm with a precision of ±0.87 %. Ignoring clustering effects, the 13,608 individuals in all 3 study arms combined will provide a precision of ±0.50 %; adding a design effect size adjustment of 2 to allow for clustering effects, the combined sample will have a precision of ±0.71.

Assuming that 5 % of individuals who demonstrate symptoms of chronic cough-/-wheeze will have a diagnosis of CAD or TB in their health passport, a sample of 453 individuals will provide an estimate of the true health burden prevalence in each individual study arm with a precision of ±2.00. Ignoring clustering effects, the 1360 individuals in all 3 study arms combined will provide a precision of ±1.17 %; adding a design effect size adjustment of 2 to allow for clustering effects, the combined sample will have a precision of ±1.64 %.

(N.B. The effects of clustering within households, within villages and within health centre catchment areas will all be fully adjusted for in the statistical analysis using multi-level modelling methods). A summary of sampling steps and estimated numbers for the baseline survey is shown in Additional file 1: [name] Additional file 1.pdf, 235 K.

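### Per-arm baseline precisions omit the protocol's own design effect of 2 (half-widths about 29 % too narrow), and the planned exact binomial intervals are not reconciled with the commitment to adjust for clustering

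*Protocol article*

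**What the plan says.** All of this stands in the protocol article, section Baseline survey.

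- **Sampling.** There are three stages: 27 health-centre clusters (9 per arm), 30 villages per cluster and 7 households per village. Every eligible person in a selected household is interviewed.
- **Formula.** The planning figures "use the approximate formula for a 95 % confidence interval ‘1.96 × standard error of prevalence estimate".
- **Interval for the analysis itself.** "In the actual analysis, exact binomial confidence intervals will be computed". The reason given for not using these intervals in planning is that they are asymmetric.
- **Per-arm precision.** For symptoms: "chronic wheeze-/-cough in each individual study arm with a precision of ±0.87" %. For a recorded diagnosis among the symptomatic: "true health burden prevalence in each individual study arm with a precision of ±2.00". Neither carries a design effect or a caveat about clustering.
- **Combined precision.** "Ignoring clustering effects, the 13,608 individuals in all 3 study arms combined will provide a precision of ±0.50" %, followed by ±0.71 at a design effect of 2. For the diagnosis outcome the pair is ±1.17 % and ±1.64 %.
- **Clustering in the analysis.** A note at the end of the section says: "The effects of clustering within households, within villages and within health centre catchment areas will all be fully adjusted for", by multi-level modelling.

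**The concern.** Two things do not fit together.

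First, in each of the two paragraphs on precision the protocol shows that it expects clustering to double the variance, but it applies this only to the combined sample. A reader who sees a labelled unadjusted figure and an adjusted figure for the combined sample will take the unlabelled per-arm figure as the precision that an arm will achieve.

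Second, an exact binomial interval in its plain form treats respondents as independent. They are not: they share households, villages and catchment areas. The closing note recognises all three levels. Taken literally, the two statements cannot both govern the same baseline estimates.

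What is at stake is how firmly the baseline values can be held. The section Sample size and sampling approach says that the present assumptions rest on expert opinion alone and will be revisited with the baseline data. Precision that looks better than it is would make the 10 % and 5 % planning values seem better established than they are.

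**Working it through.** **Inputs** (section Baseline survey): p = 10 % with n = 4,536 per arm and 13,608 combined; p = 5 % with n = 453 per arm and 1,360 combined; design effect D = 2.

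**Formula:** half-width = 1.96 × √(D × p(1 − p)/n).

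**Step 1. Reproduce the stated figures.**

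| Estimate | n | Stated, unadjusted | D = 1 | Stated, D = 2 | D = 2 |
|---|---|---|---|---|---|
| Symptoms, per arm | 4,536 | ±0.87 | 0.873 | none | **1.235** |
| Symptoms, combined | 13,608 | ±0.50 | 0.504 | ±0.71 | 0.713 |
| Diagnosis, per arm | 453 | ±2.00 | 2.007 | none | **2.838** |
| Diagnosis, combined | 1,360 | ±1.17 | 1.158 | ±1.64 | 1.638 |

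For example, 1.96 × √(0.10 × 0.90/4,536) = 0.00873, and 1.96 × √(0.05 × 0.95/453) = 0.02007. Both per-arm figures are therefore simple-random-sampling values. (The stated ±1.17 is about 1 % above the computed 1.158, which is immaterial here.)

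**Step 2. Apply the protocol's design effect to one arm.** Each arm holds 9 of the 27 clusters with the same number sampled per cluster (13,608/27 = 4,536/9 = 504). The design effect depends on the number per cluster and the within-cluster correlation, not on how many clusters are pooled. So a value of 2 carries over.

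- Symptoms: 0.873 × √2 = 1.23 points (1.2347 before rounding).
- Diagnosis: 2.007 × √2 = 2.84 points.
- Shortfall: 1 − 1/√2 = 29.3 %.

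For the 5 % planning value, the per-arm range moves from about 3.0–7.0 % to about 2.2–7.8 %.

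**Step 3. Does the exact method make up the difference?** Plain exact (Clopper-Pearson) intervals per arm are 9.15–10.92 % for symptoms and 3.2–7.5 % for diagnosis, about as narrow as the approximation. With n halved to the effective sample size they are about 8.8–11.3 % and 2.4–8.5 %. Exactness changes the shape and does not allow for clustering.

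**Step 4. Coverage if plain intervals were used and D were 2.** By normal approximation, 2Φ(1.96/√2) − 1 = 0.834. For Clopper-Pearson intervals with beta-binomial counts whose variance is twice the binomial, coverage is 0.844 (n = 4,536) and 0.856 (n = 453). Hence roughly 83 to 86 %.

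**Step 5. Sensitivity to the design effect.** As an illustration, take a between-cluster CV of 10 % (an assumption) to 25 % (the upper value that the follow-up sample-size section calls usual). Use ρ = CV² × p/(1 − p) and D = 1 + (m − 1)ρ. This counts catchment-level clustering only, before any from households and villages.

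| Outcome | m per cluster | D | Per-arm half-width |
|---|---|---|---|
| Symptoms | 504 | 1.56 to 4.49 | 1.09 to 1.85 |
| Diagnosis | 50.4 | 1.03 to 1.16 | 2.03 to 2.16 |

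A single design effect of 2 may thus be too small for symptoms and too large for diagnosis.

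**The case against.** The strongest reply is that the closing note commits the analysis to full multi-level adjustment. The exact binomial sentence is there to explain why a symmetric formula was used in planning; it concerns the shape of the interval and nowhere says that clustering will be ignored. Exact intervals on an effective sample size would satisfy both statements. This stands in part. A reader might infer that the reported baseline intervals will be about 30 % too narrow, or will cover only 83 %. The documents do not support that inference, because it assumes that the exact binomial sentence overrides the note. They do support the narrower point that the named method, as written, does not do what the note promises. The section Statistical analysis plan does not settle which governs.

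A second reply is that little depends on it. The baseline survey precedes randomisation, the combined precisions already include the design effect, and the follow-up power calculation uses the between-cluster CV and the number of clusters rather than any baseline interval width. This stands, and it limits the consequence.

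A third is that the size rests on one assumed design effect. This also stands: the 29 % holds at the protocol's own value of 2, and step 5 of the working shows how far other values could move it. It does not excuse applying that value to one set of figures and leaving it out, without comment, of the set beside them.

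The caveat and the design effect are missing from the per-arm figures however the note is read.

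**Conclusion.** The point holds in two parts.

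1. The per-arm precisions of ±0.87 and ±2.00 are understated by the protocol's own standard. At a design effect of 2 they are about ±1.23 and ±2.84 points, so the stated half-widths are about 29 % too narrow, and they are not marked as ignoring clustering. This rests only on the protocol's inputs and on equal sampling per cluster across arms.
2. The exact binomial statement and the commitment to adjust for clustering are unreconciled. Under-coverage, at roughly 83 to 86 %, would follow only if plain exact intervals were used and the design effect were near 2. It is a conditional risk, not a predicted result.

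The effect is confined to baseline description and to how firmly the planning values are held. The primary comparison and its power calculation are not touched.

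**What to change.** - **Precisions.** Restate the per-arm figures at design effect 2: ±1.23 points for chronic cough/wheeze and ±2.84 points for a recorded diagnosis. If the unadjusted values are kept alongside, label them as ignoring clustering, as is done for the combined sample.
- **Interval method.** Replace the exact binomial sentence with cluster-adjusted intervals that agree with the closing note: model-based, design-based, or exact on the effective sample size.
- **Sampling unit.** Match it to the level of the estimate. The section also gives estimation within each cluster as the survey's purpose. For an arm or the whole sample, variation between health centres may enter. For a single catchment area there is none, and the village is the first unit sampled. One rule with the health centre as primary unit would not serve both.

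The cost is a few changed sentences and a standard survey or multi-level command. The only downside is somewhat less favourable stated precision. Sample sizes and data collection do not change.
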